### Data collection instrument

Two instruments will be used for data collection:

State Trait Anxiety Inventory (STAI) [22], an instrument that assesses trait and state anxiety, the first relates to the caregiver’s usual anxiety and the second concerns transient anxiety related to some stressful event. Thus, the aim was to obtain the level of anxiety of participants before and after intervention, comparing these values to evaluate the management of anxiety by intervention, as well as comparing values between groups, evaluating the best management.Knowledge Assessment Instrument (KAI), adapted from the study by Oliveira, Souza and Pellanda [23], which has the aim of assessing the effectiveness of the multimedia strategy used in the acquisition of knowledge by participants.

This instrument has a semi-structured questionnaire composed of three stages: the first consists of sociodemographic data of participants; the second contains information about previous guidelines by other professionals and the participant’s opinion about the intervention performed in order to report whether the intervention was able to resolve doubts about the chemotherapy procedure. The third stage consists of nine questions about the chemotherapy process, to quantify the knowledge that participants obtained on the subject after intervention. The STAI and KAI are validated and reliable instruments used in studies with adults and caregivers [22, 23].

The KAI and STAI instruments will be applied as an interview, clarifying the instrument’s questions and marking the alternative chosen by the research participant. It should be noted that STAI was translated and validated into Portuguese by Biaggio, Natalício and Spielberge [22].

The Knowledge Assessment Instrument (IAC) is a form prepared by the main researcher based on the questionnaire used in the study by Oliveira, Souza and Pellanda (2016) in portuguese.

Fig 1 shows the detailed steps of the study, with SPIRIT schedule of enrollment, interventions and assessments:

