The third stage will be carried out on the second day 30 minutes after the end of interventions in which a second researcher, trained to apply the STAI and KAI and who has no understanding of patient allocation, will apply these instruments to participants of both groups, CG and EG.

A pilot test will be carried out with the first nine participants, which will serve for research analysis in order to adapt instruments and the methodological approach as necessary to meet the objectives, for better adherence to the intervention protocol.

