### Blinding

The second researcher responsible for the STAI and KAI application after intervention does not know the groups to which participants belong. In addition, data analysts will be blinded to the treatment group to which participants were randomized.

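### The KAI opinion items come before the nine scored questions in an interview by the blinded assessor, which puts that blinding at risk for the knowledge score, and for STAI only if KAI is given first

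*Protocol article*

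**What the plan says.** The Protocol article's Intervention section describes the assessment 30 minutes after the intervention: "a second researcher, trained to apply the STAI and KAI and who has no understanding of patient allocation, will apply these instruments to participants" in both groups. The Blinding section repeats the claim: "The second researcher responsible for the STAI and KAI application after intervention does not know the groups to which participants belong". It adds that "data analysts will be blinded to the treatment group to which participants were randomized".

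The Data collection instrument section sets out what this person has to do. On the mode of administration: "The KAI and STAI instruments will be applied as an interview, clarifying the instrument’s questions and marking the alternative chosen by the research participant". On the KAI: "This instrument has a semi-structured questionnaire composed of three stages". Stage one is sociodemographic. Stage two covers earlier guidance from other health staff, together with "the participant’s opinion about the intervention performed in order to report whether the intervention was able to resolve doubts about the chemotherapy procedure". Stage three is the scored part: "The third stage consists of nine questions about the chemotherapy process, to quantify the knowledge that participants obtained on the subject after intervention".

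Under Secondary outcomes, the knowledge score is the number of correct answers, from zero to nine. Under Primary outcomes, the primary outcome is STAI anxiety.

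**The concern.** The person declared blind is also the person who asks each caregiver, face to face, what they thought of the intervention they received. The two arms are easy to tell apart in conversation: a film on a tablet with a headset plus the standard guidelines, against verbal guidelines alone. The Recruitment and Initial assessment sections say that participants are told about the interventions beforehand, so they can name what they were given.

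Blinding matters here because the caregivers cannot be blinded and the main researcher delivers the education. The second researcher is the only blinded person in contact with participants when outcomes are recorded. This interviewer may clarify questions and marks the answers. One who knows the arm could, without intending it, explain a knowledge item more helpfully in one group than in the other. Blinded analysis cannot undo an influence already present in the recorded answers.

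**Working it through.** The point rests on how the provisions fit together, so these are set side by side first.

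1. **Who assesses.** One second researcher, described as unaware of allocation, applies both instruments in both arms (Intervention; Blinding).
2. **How.** By interview, with clarification allowed (Data collection instrument). The KAI is called semi-structured, which leaves room for spontaneous remarks.
3. **In what order within the KAI.** The opinion items are stage two and the nine scored questions are stage three. If the stages are applied in the order listed, any disclosure in stage two comes before the knowledge score is taken.
4. **In what order between instruments.** This is not fixed. The Intervention and Blinding sections name STAI first, while the sentence on interview mode names KAI first. Fig 1, the schedule, is not available in the text reviewed. If STAI is applied first, it is complete before the opinion items are asked.
5. **Safeguards.** The article mentions no separate collector for stage two, no self-completion, no deferral of stage two and no request to caregivers not to describe what they received.

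Steps 1 to 3 give the exposure of the KAI score. Step 4 makes the exposure of STAI conditional.

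**The plan's own figure.** The Sample size section gives d = 0.80, power 0.80, 5% significance and 26 per arm. Sidedness is not stated; two-sided is assumed. The noncentral t calculation gives n = 25.52, rounded up to 26 per arm and 52 in total, with power 0.807 at 26 per arm. The stated size is reproduced, and nothing in this point changes it.

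**Illustration of what a bias would do.** The documents give no size for interviewer bias, so the values of b below are assumptions. Suppose there is no true effect, but interviewing shifts one arm against the other by b standard deviations. A two-sided t-test with 26 per arm has 26 + 26 − 2 = 50 degrees of freedom and noncentrality b × √(26/2) = b × √13 = 3.606 × b. The probability of a significant result is then:

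| Assumed b (SD) | Noncentrality | Rejection probability |
|---|---|---|
| 0.1 | 0.36 | 6.4% |
| 0.2 | 0.72 | 10.9% |
| 0.3 | 1.08 | 18.6% |
| 0.5 | 1.80 | 42.4% |

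These figures show the effect of any bias of that size. They are not evidence that the opinion items cause one.

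**The case against.** The strongest reply is that the wording of the opinion item is not shown. Its stated purpose, to learn whether doubts were resolved, can be put identically in both arms. The Trial design section calls both arms interventions, and marking a chosen alternative fits a closed answer that needs no mention of a film. This stands in part: a reader might infer that the item necessarily reveals the arm, and the documents do not support that. They support only that disclosure is likely in some interviews, because the item is spoken and the instrument semi-structured.

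A reader might also infer that the single-blind assessment is defeated as a whole. That is not supported either. STAI is exposed only if KAI precedes it, and the order within a visit is the kind of detail a full protocol may hold. Analyst blinding is untouched.

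A third reply is that the room for influence is small: the assessor is trained, STAI has fixed response options, and KAI answers are counted as right or wrong. STAI is also the caregiver's own report, so the caregiver's knowledge of the arm remains whatever the interviewer knows. This reduces the likely size of any bias. It does not remove the route, because the interviewer may clarify the questions.

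Finally, the assumed shifts have no source in the documents. That is right, and the error rates above carry no weight in the conclusion.

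**Conclusion.** The point holds in a limited form. As described, the KAI has the assessor declared blind ask about the intervention before the scored knowledge questions, and the article states no safeguard. This puts assessor blinding at risk for the secondary outcome. For the primary outcome the risk exists only if KAI is given before STAI.

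The conclusion assumes that the three KAI stages are applied in the order listed, that the same person applies all of them, and that some caregivers will mention the film when asked for their opinion. How many would do so, and how far it would move the scores, cannot be determined from the documents. The sample size is unaffected. This is a cheap improvement worth making before recruitment, not a flaw that invalidates the design.

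**What to change.** State the order of the 30-minute assessment: STAI first, then the nine scored KAI questions, then the previous-guidance and opinion items, recorded only once the scored answers are locked. At the start, the assessor asks the caregiver not to describe what they watched or heard.

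The cost is a KAI form whose order differs from the one described. No extra staff or visit is needed. The nine-participant pilot already exists to adapt the instruments, and the Study status section says the trial is still preparing to recruit, so the new order can be introduced then.

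Two alternatives are weaker. If the main researcher collected the opinions, caregivers would be rating the education in front of the person who gave it, which invites polite answers. Paper self-completion would depart from the chosen interview mode, in a population whose schooling the Introduction notes may be limited.

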**Fig 1 pone.0285250.g001:**
[figure not shown]
Description of the study stages. P1: Day 1—admission of the child/adolescent to start chemotherapy; **P2:** Intervention Period—(Day 2). **F1:** assessment 30 minutes after intervention. KAI: knowledge assessment instrument. **STAI:** State-Trait Anxiety Inventory.

### Blinding

The second researcher responsible for the STAI and KAI application after intervention does not know the groups to which participants belong. In addition, data analysts will be blinded to the treatment group to which participants were randomized.

### Data collection and management

Researchers will ensure that the anonymity of participants is protected and data collected will remain confidential so that their identities and any type of identifying information are protected. Two copies of the informed consent form will be provided, both signed by participants, researchers and guardians.

After signing the consent form, the patient may terminate his/her participation in the study at any time, if desired, without any consequences related to his/her treatment or follow-up at the institution. The results of this research can be presented at meetings or publications; however, the identity of participants will not be revealed.

### Management of losses and dropouts

Losses and dropouts will be carefully recorded, ensuring research reliability. If any participant withdraws from participating in the study, it will be removed from the sample and another participant must be included. A logbook will be used to record information relevant to the study.

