### Sample size

The sample is probabilistic and simple random. Sample size calculation was performed using the G Power software, version 3.1.9.2 (available at: http://www.gpower.hhu.de/). The calculation was performed considering the study by Bernardi et al. [20] that evaluated the IDATE score in caregivers of children and adolescents with cancer. Thus, considering the Cohen effect size of 0.80, test power of 0.80 and significance level of 5% (p-value < 0.05), the study had 26 participants in the Control Group (CG) and 26 participants in the Experimental Group (EG), totaling a sample of 52 study participants.

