### Allocation

The randomization of participants will be carried out through the www.randomizer.org website, which will previously select participants for each group (CG and EG) by simple randomness and without the influence of researchers. The site generates a list with the sequence of participants equally divided into the two intervention groups. It is noteworthy that the allocation of participants will be carried out by a researcher who is not involved in the intervention. Additionally, the allocation will be hidden.

It is noteworthy that randomization will avoid participant selection bias and will allow groups to be compared in terms of their known and unknown risk factors.

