### Initial assessment

Participants who accept to participate in the research after signing the free and informed consent form will be presented to the study, interventions, instruments used for data collection and any doubts about the research will be cleared before intervention. After this step, participants will assigned one of two groups (CG and EG) according to the randomization list generated prior to the initial assessment.

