### Ethical considerations

The present study was analyzed and approved by the Research Ethics Committee of the Federal University of Rio Grande do Norte–UFRN–CAAE—52597121.9.0000.5537 (03/02/2022)–and CEP 5.176.784 (03/02/2022). This study was also registered in the Brazilian Registry of Clinical Trials–REBEC–RBR-4wdm8q9 as a clinical trial (03/22/2022).

The participation of patients will be carried out on a voluntary, non-profit basis and all stages, objectives, risks and benefits of the research will be explained. Participants can drop out the study at any stage without prejudice to treatment, without suffering penalties or judgments of any kind.

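### Withdrawn caregivers are removed and replaced with no cut-off at allocation, so randomised caregivers can be dropped and the STAI comparison can be biased

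*Protocol article*

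**What the plan says.** All references are to the protocol article.

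- **Management of losses and dropouts** sets the rule: "If any participant withdraws from participating in the study, it will be removed from the sample and another participant must be included". The same section adds: "Losses and dropouts will be carefully recorded, ensuring research reliability". Recording is promised, but no use of the records in the analysis is described.
- **Initial assessment** fixes when allocation happens: "After this step, participants will assigned one of two groups (CG and EG) according to the randomization list generated prior to the initial assessment". This comes after consent and before the intervention.
- **Allocation** describes the list: "The site generates a list with the sequence of participants equally divided into the two intervention groups". It adds that allocation is hidden and handled by a researcher outside the intervention, and that randomisation will prevent selection bias and make the groups comparable on known and unknown factors.
- **Data collection and management** allows withdrawal throughout: "After signing the consent form, the patient may terminate his/her participation in the study at any time, if desired". **Ethical considerations** agrees: "Participants can drop out the study at any stage without prejudice to treatment".
- **Intervention** has the STAI given before the intervention on the second day, and STAI and KAI given 30 minutes after it ends (F1 in Fig 1).
- **Data analysis** compares the groups by Student's t-test. Nothing there keeps withdrawn caregivers in the comparison.

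**The concern.** The rule is mandatory and covers any withdrawal. Read with the sections on allocation timing and on the right to withdraw, it reaches caregivers who have been randomised and may already have seen the film or heard the guidance. Who is analysed then depends on something that happens after randomisation.

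That matters for this outcome. The primary endpoint is anxiety, it is measured on the child's first chemotherapy day, and anxiety is a plausible reason for leaving. Caregivers know whether they were shown a film, so leaving could also differ by arm. If it depends on both, the remaining groups are no longer the groups that randomisation formed, and the comparability claimed in the Allocation section no longer holds. A replacement who also has to stay until F1 passes through the same filter, so refilling to 26 restores the count and not the comparison.

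The rule also discards the pre-intervention STAI of anyone who leaves after giving it. That score is the best information available for judging or correcting the loss.

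**Working it through.** **1. Does the rule reach randomised caregivers?** Order of events: consent, allocation from the existing list, pre-intervention STAI, intervention, F1. Withdrawal is open at every step. The rule names no step after which it stops applying. So it does reach them.

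**2. The plan's own sample size.** The Sample size section reads: "considering the Cohen effect size of 0.80, test power of 0.80 and significance level of 5" per cent. A two-sided two-sample t-test (noncentral t) with d = 0.80 needs 25.52 per arm, rounded up to 26, or 52 in total. Power at 26 per arm is 0.807. The stated 52 is reproduced. It carries no allowance for losses; the replacement rule stands in for one.

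**3. Worst-case size of the bias.** The documents give no dropout rate, so 5%, 10% and 20% are assumed. Further assumptions: no true effect, withdrawals in one arm only, and those leaving are exactly the fraction p with the highest F1 anxiety.

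Removing the top fraction p of a standard normal lowers the mean by φ(z₁₋ₚ)/(1−p):

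- p = 0.05: 0.1031/0.95 = 0.109 SD
- p = 0.10: 0.1755/0.90 = 0.195 SD
- p = 0.20: 0.2800/0.80 = 0.350 SD

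Against the planned 0.80 these are 14%, 24% and 44%.

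The noncentrality at 26 per arm is shift × √(26/2): 0.391, 0.703 and 1.262. With 50 degrees of freedom, the two-sided 5% test then rejects in 6.7%, 10.6% and 23.6% of trials. This ignores the smaller spread of the truncated arm. Simulation with replacement up to 26 gives about 7%, 11% and 28%.

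**4. How much of this is due to replacing?** The same scenario was simulated with 26 randomised per arm, leavers' F1 missing and nobody replaced.

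| Withdrawal in one arm | Bias, replaced | Bias, not replaced | False positives, replaced | False positives, not replaced |
|---|---|---|---|---|
| 5% | −0.11 SD | −0.11 SD | about 7% | about 7% |
| 10% | −0.19 to −0.20 SD | −0.19 to −0.20 SD | about 11% | about 10–11% |
| 20% | −0.35 SD | −0.35 SD | about 28% | about 23–24% |

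The bias is the same. Replacement adds little to the false-positive rate until losses are heavy.

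**5. Milder assumptions.** If the tendency to withdraw correlates 0.5 with anxiety, the shift halves to 0.05, 0.10 and 0.17 SD, with a false-positive rate of about 6%, 6% and 10%. If withdrawal is unrelated to the outcome, the bias is zero and the rate stays at about 5%.

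**6. Power if nobody is replaced.** At d = 0.80, two-sided 5%, equal arms: 0.79 with 50 evaluable, 0.77 with 48, 0.74 with 44. This is complete-case power and takes the losses as unrelated to outcome.

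**The case against.** The strongest reply is that the damage in step 3 is caused by absent F1 scores and that banning replacement does not bring them back. Step 4 confirms this. A reader might take the whole worst-case figure as the price of the replacement rule; it is not. What remains chargeable to the rule is that it discards randomised caregivers and their baseline STAI, presents a full 26 per arm, and so removes the means of seeing or correcting the bias.

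A reader might also infer that a replacement can only go into the vacated arm, which would be a known and non-random allocation. The documents do not establish that. The Allocation section calls the list equally divided but gives neither its length nor any replacement procedure, and it says that allocation is hidden. The limitations paragraph in the Discussion foresees recalculating the sample or extending collection. What can be said is that the drawing of a replacement is left unspecified.

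The worst case is also extreme: one arm only, and leavers perfectly ranked by a score not yet measured. The film lasts about 12 minutes, F1 follows 30 minutes after the intervention, and the children are ward patients, so losses should be few.

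Finally, the primary outcome is a reduction, and step 3 shifts the raw F1 score. If leavers are instead the most anxious at baseline, the retained arm's mean change moves by 0.35 × (1 − r) at 20% loss. With an assumed pre-post correlation r of 0.5 to 0.7, that is about 0.17 to 0.10 SD, in the opposite direction, towards less reduction. So neither the size nor the sign of a bias is known in advance.

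Each of these limits the magnitude. None supplies the missing cut-off at allocation.

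**Conclusion.** The rule as written removes and replaces caregivers after randomisation, and nothing else in the article restricts it. It can bias the STAI comparison when withdrawal depends on both arm and anxiety. The stronger statement that it does bias the result is not supported, because withdrawal unrelated to outcome produces no bias.

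The illustrative ceiling is 0.11, 0.20 and 0.35 SD at 5%, 10% and 20% one-sided withdrawal, with false-positive rates of about 7%, 11% and 24–28%. It rests on assumed dropout rates and on the most anxious leaving one arm only. The likely figure is smaller, given the two-day schedule.

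The sample size calculation itself is sound. This is a should-fix point: a poorly drawn rule on the primary comparison, cheap to repair, and with few losses expected.

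**What to change.** Replace the withdrawal sentence with wording such as:

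> Every caregiver who has been allocated stays in the allocated group and is not replaced. Data already collected are kept, F1 is sought from anyone who still agrees, and losses are reported by arm with reasons. A caregiver who leaves before allocation is revealed may be replaced, the next caregiver taking the next unused list entry.

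In Data analysis:

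- Analyse by allocated group, with F1 STAI adjusted for the pre-intervention STAI that is already collected.
- State a missing-data approach for absent F1 scores that uses that baseline, and add a sensitivity analysis for losses that depend on the unseen F1 score. Without this step the new sentence alone leaves the bias of step 4 in place.

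In Sample size, restate power for the expected evaluable number: about 0.79 at 50, 0.77 at 48, 0.74 at 44.

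The cost is protocol wording and a slightly lower stated power. No extra visit or measurement is needed.
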